The first parameter (chemokines mRNA) is particularly important since the blockage of cellular co-receptor such ad CCR5 could also influence the process of internalisation of -chemokines. Phenotypes on the cell surface will be evaluated through cytofluorimetry (fluorescein isothiocyanate [FITC], phycoerytrin [PE], and phycoerytrin-cyanin 5 [PCy5]). CD45RA/CD62L/CD4, CD4/CD38, CD8/CD38 in order to measure naïve, memory, and activated CD4+ and CD8+ will be analyzed. The proliferation of T lymphocytes will be evaluated through the quantification of the expression of the Ki67 nuclear antigen in CD4+ and CD8+ cells (an antigen which is expressed during the proliferation phases of cell cycles).

The *ex-vivo* characterization ofsystem IL-7/IL-7R homeostasis will be carried out as well.

If available, a sample before first-line HAART will be analyzed for tropism.

Sample size and statistical analysis

This will be a pilot controlled clinical trial.

Sample size: assuming a proportion of "responder" patients (those patients who achieve, in 2 consecutive measurements, CD4> 200 cells/µL and CD4 lymphocytes recovery > 25 % from baseline, maintaining HIV-RNA <50 copies/mL) of 5% in the control arm, it is expected an absolute increase δ = 20% in the arm of intensification with MVC (responder patients with maraviroc = 25%). We have fixed the study power 1-β = 80% and α = 0.05, thus it is necessary to randomize 50 patients per arm, taking into consideration any protocol violations/lost to follow-up. The threshold of 20% difference between treated with MVC or non-treated is compatible with a proof of efficacy indicated by immunological trials with antagonists of CCR5 co-receptor.

A ​​1:1 randomization in blocks stratified by center will be made.

For statistical analysis, depending on the indication, the following tests will be carried out: chi-square test according to Mantel-Haenszel test, Kruskal Wallis, Log-rank test and Kaplan-Meier analysis model multivariate Cox and logistic regression .

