Comparison of CD4+ and CD8+ count between the study arms A and B and at the different time-points will be assessed by t-test for independent and dependent samples respectively in an intention to treat (ITT) analysis. Statistical evaluation of simple and composite endpoints will be analyzed by binary logistic regression models for the odds ratio estimation and the related 95% confidence intervals. Odds ratios of the MVC arm will be controlled in the regression models for CD4+ counts at baseline. Statistical significance level will be estimated by Wald test and was set at .05 for all of the analyses. In the per-protocol (PP) analysis, patients who dropped the study or switched treatment will be included until their last observation in the randomization arm.

Immunological parameters at baseline (T0), after 12 (w12) and 48 weeks (w48) of MVC intensification will be analyzed with GraphPad 5 PRISM software. Wilcoxon and Mann-Whitney U test will be used. All tests are 2-sided and differences will be considered statistically significant at p<0.05.

Withdrawal from the study

The motivation and the exit date from the study will have to be reported in the medical record of each patient.

The study participants are free to withdraw from the participation at any time, without any explanation and without any prejudice against any and/or future care that should be applied in the Clinical Center where they are followed.

Also, the study participants can be requested to withdraw from the study at any time at the discretion of the investigator, if participation in the study involves any kind of risk for the patient’s health.

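### Randomisation is stratified by centre but the endpoint analysis names only baseline CD4; a centre-stratified Mantel-Haenszel test would follow the design at almost no cost (minor)

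*Protocol*

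**What the plan says.** All of this stands in the protocol under Sample size and statistical analysis, unless noted.

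- **Design.** 1:1 "randomization in blocks stratified by center will be made". No block size is given. The Design section lists about nine centres, or ten if two divisions of one hospital count separately.
- **Endpoint analysis.** "Statistical evaluation of simple and composite endpoints will be analyzed by binary logistic regression models for the odds ratio estimation". On covariates: "Odds ratios of the MVC arm will be controlled in the regression models for CD4+ counts at baseline". On the test: "Statistical significance level will be estimated by Wald test and was set at .05 for all of the analyses".
- **CD4 and CD8 counts.** Comparisons between arms and between time-points "will be assessed by t-test for independent and dependent samples respectively in an intention to treat (ITT) analysis".
- **A possible stratified test.** A general list of methods, to be used as the situation requires, includes a "chi-square test according to Mantel-Haenszel test". It is tied to no endpoint and names no stratum variable.
- **Planning assumption.** A responder proportion "of 5% in the control arm, it is expected an absolute increase δ = 20% in the arm of intensification with MVC", and "We have fixed the study power 1-β = 80% and α = 0.05", giving 50 patients per arm.

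Centre enters no analysis that the protocol describes.

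**The concern.** Blocking within centre gives both arms nearly the same mix of centres. If centres differ in response, the responder counts in the two arms then rise and fall together, and their difference varies less than two independent binomial samples would. A model without centre computes its standard error as if the samples were independent. That standard error is too large for the estimate it accompanies, so under the null the test rejects less often than 5%. Under the alternative, leaving out a prognostic factor also pulls the odds ratio towards 1.

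At stake is power. The trial takes the trouble to stratify and then does not use the strata, and the sample size has little slack (shown in the working).

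**Working it through.** **1. The plan's own figure.** Inputs from the protocol: 5% versus 25%, power 80%, alpha 0.05, two-sided. With pooled variance, mean proportion 0.15 and no continuity correction:

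n = [1.960 × √(2 × 0.15 × 0.85) + 0.842 × √(0.05 × 0.95 + 0.25 × 0.75)]² / 0.20² = (0.990 + 0.408)² / 0.04 = 48.8, so 49 per arm.

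The stated 50 is reproduced; power at 50 per arm is 80.9%. Since 49 / 0.98 = 50, there is room for about 2% loss. Expected responders: 50 × 0.05 + 50 × 0.25 = 2.5 + 12.5 = 15.

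**2. Simulation of the planned model and alternatives.** Assumptions not in the documents: nine centres of 11 or 12 patients, blocks of 4, baseline CD4 log-odds 0.8 per SD, normal centre effects on the logit with SD 0 to 1.5. There were 3,000 trials per scenario, with all tests applied to the same trials. Monte Carlo standard error is about √(0.05 × 0.95 / 3000) = 0.4 points for type I error and √(0.84 × 0.16 / 3000) = 0.7 points for power.

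The Mantel-Haenszel statistic sums over centres k, with n_k patients, n_1k on maraviroc, m_k responders and a_k responders on maraviroc:

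χ² = [Σ(a_k − n_1k m_k / n_k)]² / Σ[n_1k (n_k − n_1k) m_k (n_k − m_k) / (n_k² (n_k − 1))].

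Type I error (%), 15% response in both arms:

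| Test | SD 0 | SD 0.5 | SD 1.0 | SD 1.5 |
|---|---|---|---|---|
| Logistic Wald, CD4 only (as planned) | 4.5 | 4.3 | 4.0 | 1.9 |
| Logistic Wald, CD4 and centre | 5.7 | 5.6 | 5.6 | 4.7 |
| Chi-square, unstratified | 4.7 | 5.3 | 4.8 | 3.4 |
| Mantel-Haenszel by centre | 4.8 | 5.5 | 5.7 | 5.1 |

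Power (%), 5% versus 25%:

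| Test | SD 0 | SD 0.5 | SD 1.0 | SD 1.5 |
|---|---|---|---|---|
| Logistic Wald, CD4 only (as planned) | 75.3 | 74.5 | 74.2 | 70.1 |
| Logistic Wald, CD4 and centre | 76.8 | 76.7 | 77.0 | 72.4 |
| Chi-square, unstratified | 83.4 | 83.0 | 83.9 | 84.0 |
| Mantel-Haenszel by centre | 83.5 | 83.6 | 85.2 | 87.5 |

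A run with nine unequal centres of 4 to 24 patients (8,000 trials per scenario) gave, for the planned model, type I error of 3.7 / 3.5 / 3.2 / 2.5% and power of 75 / 75 / 73 / 69%. So the planned model's type I error is 3.2-4.0% at SD 1.0 and 1.9-2.5% at SD 1.5.

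**3. What the strata alone are worth.** Compare Mantel-Haenszel with the unstratified chi-square, two tests of the same kind. In the table above the power differences are +0.1 / +0.6 / +1.3 / +3.5 points. A separate simulation (nine centres, blocks of 4) gave:

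- SD 0: 84.4 − 85.2 = −0.8
- SD 0.5: 84.5 − 84.6 = −0.1
- SD 1.0: 86.3 − 84.5 = +1.8
- SD 1.5: 88.4 − 85.3 = +3.1

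Together this is about −1 to +3 points, and about nil at SD 0.5.

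**4. Where the larger gap comes from.** Split the distance from the planned model to Mantel-Haenszel, using the power table:

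- SD 0: 83.5 − 75.3 = 8.2 points, of which 83.4 − 75.3 = 8.1 separate the planned model from the unstratified chi-square.
- SD 1.0: 85.2 − 74.2 = 11.0, of which 83.9 − 74.2 = 9.7.
- SD 1.5: 87.5 − 70.1 = 17.4, of which 84.0 − 70.1 = 13.9.

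The gap is already 8 points with no centre effect. An exact calculation with 50 per arm, no centres and no covariate points the same way: power 85.2% for chi-square and 73.9% for Wald. With 5% response in both arms and no centre effect, the planned model rejects in 0.4% of trials and the unstratified chi-square in 4.3%. Within the Wald framework, adding centre gains only 1.5 / 2.2 / 2.8 / 2.3 points.

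**5. Why not centre indicators.** At 5% versus 25%, at least one centre had no responder in 77-98% of simulated trials. Mantel-Haenszel handles such centres without estimating a parameter for each.

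**The case against.** **The effect may be negligible.** This largely stands. The documents say nothing about how much centres differ. With 15% overall response, SD 1.0 implies centre rates from about 2% to 49% (95% range), and SD 1.5 from about 0.5% to 65%, so the larger gains need strong heterogeneity. With 60 of the 100 patients at one centre (an assumption), SD 1.0 gives 80.7% unstratified and 81.5% stratified, a gain of 0.8 points.

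**This could be left to the analysis plan.** In part. The protocol does not say that baseline CD4 is the only covariate, and naming the stratum of a listed test is often left to that plan. But the protocol itself fixes the model, the named covariate and the test for these endpoints, and that choice does not follow its own randomisation. The general Mantel-Haenszel entry does not repair this, because the endpoints are then assigned to logistic regression.

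**Stronger readings that the documents do not support.**

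- A reader might infer that ignoring the strata makes the analysis invalid or too liberal. The error runs the other way: the planned test rejects too rarely.
- A reader might put the whole shortfall against 84-88% power down to the omitted strata. Most of it is present with no centre effect and belongs to the Wald test with few responders.
- A reader might call this a flaw in the primary comparison. The protocol lists a simple and a composite endpoint without ranking them, so the point concerns both.

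**Conclusion.** The mismatch is real and minor. The analysis fixed for both endpoints leaves out the factor used to stratify the randomisation, and is somewhat conservative if centres differ. Stratifying by centre is worth about −1 to +3 points of power and keeps type I error near 5%. The shortfall in type I error without strata becomes clear only when centres differ strongly.

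These sizes rest on assumed centre numbers, block size, CD4 effect and between-centre SD. The power figures apply to the responder definition in the sample-size paragraph, which also requires maintained viral suppression; the protocol gives no response rates for the simple endpoint. Confidence is high in the text and the direction, moderate in the size. The planned analysis does not inflate false positives, so this is a cheap improvement and not a threat to the trial's conclusions.

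**What to change.** State that the significance test for the simple and the composite endpoint is the Mantel-Haenszel chi-square stratified by randomising centre. Report it with a Mantel-Haenszel risk difference and 95% confidence interval, using a variance that is valid for sparse strata. Keep the logistic odds ratio adjusted for baseline CD4 as supportive, and say that the stratified test decides if the two disagree. Do not add a separate indicator for each centre to the logistic model.

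For the between-arm CD4 comparison, now an independent-samples t-test, add centre, for example as a factor in a linear model with arm.

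Cost: a sentence or two, using a method already listed and no extra patients or data. The downside is up to about 1 point of power if centres do not differ; the worst simulated case, ten centres with exact 5/5 balance, was 85.0% to 83.6%, or 1.4 points. Replacing the Wald test also recovers the larger loss shown in the working, which is a benefit separate from the strata.

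### The trial is sized on an absolute difference in responders, but the only effect estimate fixed is an odds ratio with a Wald test, which is imprecise and sometimes not estimable at the planned rates

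*Protocol*

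**What the plan says.** Under Sample size and statistical analysis (Protocol, Study Methodology), planning is on the absolute scale. The responder proportion is taken as "of 5% in the control arm, it is expected an absolute increase δ = 20% in the arm of intensification with MVC", with the result given in per cent as "responder patients with maraviroc = 25". The error rates are "We have fixed the study power 1-β = 80% and α = 0.05", and the conclusion is "thus it is necessary to randomize 50 patients per arm", "taking into consideration any protocol violations/lost to follow-up". The choice of difference is defended with the remark that "The threshold of 20% difference between treated with MVC or non-treated is compatible with a proof of efficacy" as seen in earlier trials of this drug class.

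The analysis text that follows turns to another scale. Both the simple and the composite endpoint are to be analysed by "binary logistic regression models for the odds ratio estimation and the related 95% confidence intervals". The maraviroc odds ratio is adjusted for baseline CD4, and significance is by Wald test at 0.05. A Mantel-Haenszel chi-square appears in a general list of methods, but it is a test and is not tied to an endpoint. The protocol nowhere names a difference in responder proportions or its confidence interval, and nowhere says what happens if one arm has no responders.

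**The concern.** Two things follow from pairing this design with this analysis.

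The first is scale. A reader who wants to set the result beside the planning assumption needs a difference in proportions and its interval. The planned output is an odds ratio conditional on baseline CD4. It corresponds to a given difference only once the control rate is known, and its confidence limits do not convert into limits for the difference.

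The second is sparse data. At 5% of 50 patients, the control arm is expected to supply 2.5 responders. The log odds ratio and its Wald test behave poorly with so few events. With no control responder the maximum-likelihood odds ratio is infinite and the Wald test gives no usable answer, although nearly all such trials favour maraviroc clearly. The stated method can therefore fail just where the result is most convincing.

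**Working it through.** **Inputs.** From the sample-size text: control 5%, maraviroc 25%, α 0.05, power 80%, 50 per arm. Two-sided testing is assumed for the sample size. The protocol states it in the paragraph on immunological parameters ("All tests are 2-sided and differences will be considered statistically significant at p<0.05"). The 5% and 25% belong to the sample-size definition of a responder, which adds sustained viral suppression to the composite endpoint. I apply them to the composite endpoint as they stand. No rates are given for the simple endpoint.

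**1. The plan's own figure.** Pooled-variance formula, no continuity correction, mean rate 0.15:

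n = [1.96·√(2·0.15·0.85) + 0.842·√(0.05·0.95 + 0.25·0.75)]² / 0.20² = (0.990 + 0.408)² / 0.04 ≈ 48.8, so 49 per arm.

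This agrees with the stated 50. The approximate power at 50 per arm is 80.9%. The sample size was therefore built on a comparison of two proportions.

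**2. Odds ratio at plan values.**

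- OR = (0.25/0.75)/(0.05/0.95) = 6.33.
- Expected counts are 2.5 of 50 and 12.5 of 50, so SE(log OR) = √(1/2.5 + 1/47.5 + 1/12.5 + 1/37.5) = 0.726.
- 95% CI = exp(1.846 ± 1.96·0.726) = 1.5 to 26.3.

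**3. Risk difference at plan values.** 0.20 ± 1.96·√(0.05·0.95/50 + 0.25·0.75/50) = 0.20 ± 0.134, that is 6.6 to 33.4 points.

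**4. What an odds ratio of 6.33 means in points.** With control rate p, the treated odds are 6.33·p/(1−p). Control rates other than 5% are assumed for illustration.

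| Control rate | Difference implied by OR 6.33 | OR that a 20-point gain would give |
|---|---|---|
| 2% | 9.4 points | 13.8 |
| 5% | 20.0 points | 6.33 |
| 10% | 31.3 points | 3.86 |
| 15% | 37.8 points | 3.05 |

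A significant odds ratio does not fix the difference either. Responders of 2/50 against 9/50 give OR = (9·48)/(2·41) = 5.27 (1.08 to 25.8), Wald p = 0.040, and a difference of 14 points.

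**5. How often the odds ratio fails.** P(no control responder) = 0.95^50 = 7.7%. Adding baseline CD4 to the model does not help, because the treatment coefficient still diverges. By contrast, 0/50 against 12/50 has a difference of 24 points with a Newcombe 95% CI of 12.0 to 37.4.

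**6. Exact power at 5% v 25%, 50 per arm.** Every pair of binomial counts is enumerated, and results significant in favour of maraviroc are counted (unadjusted analyses).

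| Method | Power |
|---|---|
| Wald test of log OR, zero-cell samples counted as non-significant | 73.9% |
| Newcombe interval for the difference excludes 0 | 82.4% |
| Uncorrected chi-square | 85.2% |

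In nearly all zero-cell samples the Newcombe interval excludes 0. Using it there gives 73.9 + 7.7 = 81.6%, so most of the gap comes from those samples. With 45 evaluable per arm (an assumed loss of 10%), the Wald figure falls to 65.9% and zero-cell samples rise to 9.9%.

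**7. Is 20 points a workable pass mark?** At the design rates the observed difference is at least 20 points with probability 55%.

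**The case against.** The strongest reply is that sizing on two proportions and analysing by covariate-adjusted logistic regression is ordinary practice. Both address the same null hypothesis, and an adjusted odds ratio with an interval is a legitimate summary. An analysis plan that is not shown may add absolute measures. This stands: the pairing is not a contradiction, and the scale difference alone would be a minor reporting matter.

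A reader might infer that the trial cannot say whether 20 points was reached. The documents do not support that. The endpoint is binary in two randomised arms, so the crude difference follows from the counts (12/50 − 2/50 = 20 points). The range in the conversion table arises only while the control rate is unknown. What is missing is a pre-specified difference with its interval.

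A reader might also take 20 points as the protocol's definition of efficacy, since it uses the word threshold. But the increase is described as expected, the remark justifies its size from outside trials, and the decision rule is the Wald test at 0.05. A mark met only 55% of the time at the design rates cannot be the success criterion of a trial planned at 80% power.

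The power figure has limits too. It is unadjusted, and adjustment for baseline CD4 could change it in a way the documents do not allow me to calculate. It also treats zero-cell samples as failures, where an analyst would probably improvise another method. But that choice would then be made after seeing the data, because the protocol names none.

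**Conclusion.** The concern holds in limited form. The protocol fixes model, covariate, effect measure and test for the responder endpoints, and that choice suits the planned event rate poorly. At plan values the odds ratio has an interval of about 1.5 to 26 and cannot be estimated in about 8% of trials. Its unadjusted Wald test has about 74% exact power if those trials count as non-significant, against the 80% on which the trial was sized. A Newcombe interval for the difference has about 82%, and it is on the scale of the planning assumption.

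These figures assume true rates of 5% and 25%, all 50 patients per arm evaluable and no covariate adjustment. With a higher control rate the sparse-data problem shrinks, while the need for a stated absolute difference remains. The sample size is not in error on this point, and 20 points is a planning difference, not a success rule.

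**What to change.** In the analysis text of Sample size and statistical analysis:

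- Pre-specify, for both responder endpoints, the proportion in each arm and their difference (maraviroc minus control) with a 95% CI that remains valid with zero cells. A Newcombe or score-type interval would do, or a centre-stratified Mantel-Haenszel risk difference, since randomisation is stratified by centre. Report it beside the adjusted odds ratio.
- State that this interval is used if the logistic model is separated. Standardising the logistic model is not a safe substitute there, because it rests on the same failed fit.
- Say in advance whether the difference or the odds-ratio test governs the conclusion when the two disagree.
- Describe 20 points as the planning benchmark for reading the interval. At plan values the interval is about 7 to 33 points, so the trial could not confirm an effect of at least 20.

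The cost is a few sentences and a little code, on data already to be collected, with the sample size unchanged. The small downside is that a simple or centre-stratified difference is not adjusted for baseline CD4 and may occasionally disagree with the odds-ratio test, which is why the governing analysis must be named.

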## Objectives

Primary objectives:

- Evaluate the **clinical (defined as protection from the onset of opportunistic infections) and immunological efficacy** of HAART intensification with MVC as treatment of HIV-1 infection in patients with a CD4 count ≤ 200 cells/L and/or a recovery of CD4 cells < 25% compared to the HAART initiation and with a complete and stable virologic suppression after 12 months of HAART. Patients could also being included if their CD4 slope has been stable without any improvement, with an absolute value around 200 cells/L;
- Evaluate the effects of HAART intensification with MVC on the modification of **immunologic and virologic parameters**;
- Evaluate the **tolerability** of HAART intensification with MVC and the appearance of drug-related side effects.

Secondary objectives:

- Evaluation of intensification treatment of HAART with MVC on modification of following immunological parameters: chemokines-mRNA analysis, helper memory and naïve CD4 lymphocytes, IL-7/IL-7R homeostatic system.

Endpoints

- Simple endpoint: achievement of CD4 count > 200/µL in two consecutive measurements;
- Composite endpoint: CD4 counts > 200/µL and recovery of CD4 > 25% at 2 consecutive time-points (w12 and w48).

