## Design

This will be a randomised, multicenter, study that will evaluate HAART intensification with MVC as treatment of HIV-1 infection in patients with a CD4 count ≤ 200 cells/L and/or a recovery of CD4 cells < 25% compared to the HAART initiation and/or a stable CD4 slope without any improvement, with an absolute value around 200 cells/L and with a complete and stable virologic suppression after 12 months of HAART. Among the adult HIV-1 infected patients screened, 50 patients will be randomized in arm A (HAART + MVC) and 50 in arm B (HAART without MVC), in a 1:1 fashion.

Treatment regimen

Maraviroc dosing schedule is: from 150mg to 600mg BID, according to the other antiretroviral drugs in the patient.s therapy. Maraviroc will be administered at the dosing regimen of 150mg BID with nelfinavir and protease inhibitors boosted by ritonavir (PI/r), as example atazanavir/rtv, darunavir/rtv, lopinavir/rtv e saquinavir/rtv; 300mg BID with nevirapine, fosamprenavir/rtv, tipranavir/rtv, raltegravir and enfuvirtide (T-20); 600mg BID with efavirenz and etravirine. In the case of administration within a regimen including a PI/rtv (atazanavir/rtv, darunavir/rtv, lopinavir/rtv e saquinavir/rtv), MVC dosage will be always 150mg BID.

Study population

The enrollment of 100 continuously observed patients, with the characteristics mentioned above, at Clinical Science Department, Division of Infectious Diseases and Immunopathology of Università degli Studi, “L. Sacco” Hospital, Milan, is expected after EC/IRB approval.

Other clinical centers will participate to the study: Clinic of Infectious Diseases, “San Paolo” Hospital: Prof.ssa [name]; 1a and 2a Division of Infectious Diseases, “L. Sacco” Hospital, Milan: [name]; Clinic of Infectious Diseases, Scientific Institute “San Raffaele” Hospital, Milan: [name]; Clinic of Infectious Diseases, University of Brescia: [name]; Clinic of Infectious Diseases, University Tor Vergata, Rome: [name]; Clinic of Infectious Diseases, University of Turin: [name] [name]; National Institute of Infectious Diseases, “L. Spallanzani” Hospital, Rome: [name]; Clinic of Infectious Diseases, “San Gerardo” Hospital, Monza: [name].

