**Study Methodology**

Clinical evaluation.

At baseline, at weeks 2, 4, 8, 12 from the beginning of the study, following 4, 6 and 9 months from the beginning of the study and at the end of the period of administration of MVC:

- Clinical History;
- Physical Examination;
- Evaluation of Karnofsky index

Blood tests

At enrollment and subsequently at weeks 2, 4, 8, 12 from the beginning of the study, and then at 4, 6 and 9 months from the beginning of the study and at the end of the period of administration of MVC:

- Examination of complete blood cell count with differential;
- Blood tests: glucose, urea nitrogen, creatinine, electrolytes, transaminases, GT, direct and indirect bilirubin, amylase, LDH, CPK, sieroprotein electrophoresis, hsPCR, total cholesterol and HDL;
- Pregnancy test at enrolment.

Virological evaluation

At screening and in case of virologic failure during the protocol, it will be performed a blood test to get 2 aliquots of 5x10^6 frozen viable cells in order to perform the sequence of the gp120 gene and subsequent determination of viral tropism by algorithm .

It will also be required, where available, plasma stored under appropriate conditions, from the patient when in a condition of detectable viremia (2 mL of plasma required to perform the test Trofile post-hoc).

At baseline and after 2, 4, 8 and 12 weeks after start of the study, and then at 4, 6 and 9 months from the beginning of the study and at the end of the period of administration of MVC:

- Quantification of HIV-RNA.

Immunological evaluations

At baseline and after 2, 4, 8, 12 weeks after start of the study, then at 4, 6 and 9 months from the beginning of the study and at the end of the period of administration of maraviroc:

- Immunophenotypic analysis (lymphocytes memory and naïve CD4 & CD8);

- Analysis of chemokine mRNA;

- Analysis of the levels of plasma IL-7/IL-7R.

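### The withdrawal paragraph offers a patient at risk only exit from the study, and no follow-up is planned once MVC is stopped early, so week-48 and side-effect outcome data are lost

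*Protocol*

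**What the plan says.** The subsection on withdrawal, within Study Methodology, gives two exits. Participants may leave freely at any time. In addition, "the study participants can be requested to withdraw from the study at any time at the discretion of the investigator", the condition being "if participation in the study involves any kind of risk" to the patient's health. On documentation it asks for one thing: "The motivation and the exit date from the study will have to be reported in the medical record of each patient".

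Other parts of the protocol bear on this:

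- **Design:** "50 patients will be randomized in arm A (HAART + MVC) and 50 in arm B (HAART without MVC), in a 1:1 fashion". No placebo and no blinding are described.
- **Objectives:** the primary objectives include protection from opportunistic infections, immunological and virological parameters, and the tolerability "of HAART intensification with MVC and the appearance of drug-related side effects". The composite endpoint uses CD4 at weeks 12 and 48.
- **Study Methodology, visits:** clinical, blood, virological and immunological assessments run to a last visit placed "at the end of the period of administration of MVC".
- **Statistical analysis:** CD4 and CD8 counts are compared between arms "in an intention to treat (ITT) analysis". For the per-protocol analysis, "patients who dropped the study or switched treatment will be included until their last observation in the randomization arm".

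**The concern.** Stopping a study drug and leaving a study are different events, and the withdrawal paragraph provides only for the second. If a site follows it as written, a patient whose MVC is stopped for a side effect leaves the study and has no further planned assessments. The visit schedule does not help, because its last visit moves with the end of MVC.

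Two things are at stake. First, an ITT comparison needs outcomes on everyone randomised. A patient who leaves before week 48 has no week-48 CD4 or HIV-RNA value and can be classified on the composite endpoint only by convention. Second, tolerability and protection from opportunistic infections are primary objectives. How a side effect resolved, whether others followed, and whether an infection occurred after exit would all be unknown. A statistical analysis plan can choose how to handle missing values, but it cannot recover data that sites were never asked to collect.

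**Working it through.** **Step 1. Passages side by side.**

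| Question | What the protocol provides |
|---|---|
| Exit for a patient at risk | Withdrawal from the study, at the investigator's discretion |
| Recorded at exit | Reason and date |
| Stopping MVC while remaining under observation | Not described |
| Data collection after exit | Not forbidden, not planned |
| Last visit | Tied to the end of MVC administration |
| Treatment change as distinct from dropout | Named once, in the per-protocol sentence, with data kept to the last observation |

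The triggering side effect is therefore captured through the recorded reason. What follows it is not.

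**Step 2. The plan's own sample size.** Inputs from the sample size paragraph: 5% v 25% responders, α = 0.05, power 80%; tests are two-sided. The pooled normal formula without continuity correction gives 49 per arm, which agrees with the stated 50. Power at 50 per arm is 80.9% by the same approximation. Since 49/0.98 = 50, the figure leaves room for a loss of about 2%.

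**Step 3. Illustration of size.** The protocol gives no exit rate. Assume that a share w of arm A exits (10% or 20%, that is 5 or 10 of 50) and none of arm B. Patients who stay on MVC respond at 25%; those who stop would respond at rate r.

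- Exits counted as non-responders: 0.25 × (1 − w).
- Exits dropped from the denominator: 0.25.
- Exits followed to week 48: 0.25 × (1 − w) + r × w.

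| Arm A rate | w = 10% | w = 20% |
|---|---|---|
| Counted as non-responders | 0.25 × 0.90 = 22.5% | 0.25 × 0.80 = 20.0% |
| Dropped | 25.0% | 25.0% |
| Followed, r = 5% | 22.5% + 0.5% = 23.0% | 20.0% + 1.0% = 21.0% |
| Followed, r = 25% | 22.5% + 2.5% = 25.0% | 20.0% + 5.0% = 25.0% |

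So follow-up recovers 0.5 to 1 point if stoppers respond like controls, and 2.5 to 5 points if they respond like patients still on MVC. Dropping them overstates the followed rate by 2 to 4 points when r = 5%, and not at all when r = 25%.

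**Step 4. Power against 5% in arm B, 50 per arm, two-sided 0.05, exits counted as non-responders.**

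| Arm A rate | Normal approximation | Exact, uncorrected chi-square | Exact, unadjusted Wald test |
|---|---|---|---|
| 25% | 80.9% | 85.2% | 73.9% |
| 22.5% | 72.6% | 77.1% | 64.3% |
| 20% | 62.4% | 66.4% | 52.1% |

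The Wald column is closest to the planned logistic regression, but omits its adjustment for baseline CD4 and counts tables with an empty cell as not significant. The loss is similar in each column: about 8 to 10 points at w = 10% and 18 to 22 at w = 20%.

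**Step 5. Tolerability, illustration only.** Suppose 10% of arm A exit, and the risk of a later side effect is 30% in them and 10% in the others. The true risk is 0.10 × 0.30 + 0.90 × 0.10 = 12%. Without follow-up, 0.90 × 0.10 = 9% would be counted over all 50, or 10% among those remaining.

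**The case against.** The strongest reply is that the paragraph is a permissive safety clause. It says that a patient can be asked to leave. It does not say that stopping MVC requires leaving, and it does not forbid later data. The per-protocol sentence separates those who left from those who changed treatment, so the authors did foresee the second case. All of this is correct. But that sentence is an analysis rule that ends at the last observation. It schedules nothing, and no other passage does.

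A reader might infer that the rule acts almost only on arm A. The text does not establish that. It is worded for both arms, and an arm B patient with virological failure or an opportunistic infection could also be asked to leave. What stands is a likelihood: arm B adds visits and blood tests to existing HAART, so risk from taking part lies mainly with MVC, and nothing described conceals the arm.

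A reader might also infer that tolerability cannot be assessed, or that the rule contradicts ITT. Neither follows. The objective speaks of side effects appearing, and one that prompts exit has already appeared and is recorded. Analysis by randomised arm remains possible, and the handling of missing values may properly be left to an analysis plan. The loss is of the data such an analysis would use.

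Finally, under the assumptions above much of the fall in power comes from stopping MVC itself. If stoppers respond at 5%, follow-up gives 23% or 21% against 22.5% or 20%. That stands, and it limits what the fix can gain on the responder endpoint.

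**Conclusion.** The point holds as a gap in planned data collection that sits badly with the protocol's ITT statement and primary objectives. For a patient at risk the protocol provides only exit from the study, and nothing plans observation after MVC is stopped early. The resulting losses are likely, not certain, to fall more on arm A and to be related to tolerability.

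Their size cannot be derived from the document. The 22.5-20% responder rate rests on three assumptions: 10-20% exits in arm A, none in arm B, and exits counted as failures. It would be tempting to say that the clause moves the estimate by −5 to +5 points. The documents do not support that range, because its ends need different response assumptions. The lower end lets removed patients respond at 25%: 0.25 × 40/50 = 20%. The upper end lets them respond at 5% within an arm averaging 25%, and drops them: (12.5 − 0.5)/40 = 30%. With 5% and the same arm average kept throughout, counting them as failures gives (12.5 − 0.5)/50 = 24%, a shift of 1 point. The direction and size of any bias depend on outcomes that would not be observed, which is the reason to collect them. The change is worth making because it is cheap and data missed during the trial cannot be recovered.

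**What to change.** Reconcile the withdrawal paragraph with the ITT statement, the per-protocol wording on treatment switches and the visit schedule, by separating the end of study drug from the end of observation. As a data-collection rule only:

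- Patients who stop MVC, and who agree to continue, keep the already scheduled assessments (CD4, HIV-RNA, opportunistic infections, side effects) to week 48.
- Week 48 is counted from randomisation in both arms, not from the end of MVC administration.
- The outcome of a side effect that led to stopping is recorded.
- These patients are analysed in their randomised arm.

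When and why MVC is stopped, and any withdrawal for safety, stay with the investigator; no clinical rule is proposed.

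The cost is about one amended paragraph and a few more visits for patients off MVC, using assessments already in the schedule. Off-treatment values will enter the ITT analysis and may slightly dilute the effect.
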